#### Secondary outcomes.

**Inflammatory and pro-resolving profile:** Behind the symptoms of PCC lies an unresolved inflammatory cascade. Since SPMs are considered to be pro-resolving inflammation, it was considered to analyze the change in this inflammatory profile [25–27]. The analyzed parameters will be: cytokines: IL-1, IL-2, IL-4, IL-6, IL-8, IL-10, IL-17A TNF-α, and interferon-gamma (IFN-γ); free fatty acids: EPA, DHA, arachidonic acid (ARA), (DPA) and monohydroxylated lipid mediators (LMs): 17-HDHA, 18-HEPE, 14-HDHA; resolvins (Rv): EPA-derived RvE1, RvE2 and DHA-derived resolvins (RvD): RvD1, RvD2, RvD3, RvD4, and RvD5; maresins (MaR): MaR1, and MaR2; protectins: PD1 and PDX; lipoxins (LX): LXA4, and LXB4; prostaglandins: PGE2, PGD2 and PGF2α; thromboxane TXB2; and leukotriene LTB4.

Blood samples for cytokine analysis, will be centrifuged for 15 minutes at 1000 x g. Then, the serum will be removed, aliquoted and stored at −80°C until cytokine measurement. IL-6 will be measured by enzyme-linked immunosorbent assay using the Quantikine® HS Human Immunoassay Kit (HS600C, R&D systems) according to the manufacturer’s recommendations by using a Biotek Synergy HT Microplate Reader. The rest of the cytokines will be determined by using the Human XL Cytokine Luminex® Kit Performance Assay (FCSTM18B, R&D Systems) according to the manufacturer’s recommendations and analyzed with a LABScan 100 Multiplexing Analyzer System (Luminex Corporation).

Plasma and serum samples for free fatty acids and lipid mediator determinations will be collected and processed as previously described by Regidor et al. 2022 [28]. In brief, peripheral blood samples will be collected and immediately centrifuged at 120 g for 20 min with free stop. Plasma supernatant will be transferred to 1.5 mL tubes, topped with nitrogen gas, capped, and immediately stored at −80°C for further processing. Serum samples will be generated as Norris et al. 2017 [29]. In brief, after an overnight incubation at 37°C, the same protocol described for plasma will be applied. Then, for LMs extraction, a solid-phase extraction (SPE) method will be performed as follows: 4 mL of methanol containing 500 pg. of each internal labelled standard (d8-5-HETE, d5-RvD2, d5-LXA4, d4-LTB4, and d4-PGE2, Cayman Chemical Company) will be added to enable ulterior samples LMs quantification. Calibration curves will register using synthetic and authentic LM mixtures. After that, a protein precipitation phase will take place (−80°C, 30 min) and posterior centrifugation at 2000 g, 10 min, 4°C. In addition, the supernatant will be acidified to pH = 3.5 just before loading onto a conditioned-SPE column (Biotage) and pH neutralized with MilliQ water, followed by an n-hexane wash step. After that, lipid elution will take place with 9 mL of methyl formate. Finally, extracts from the SPE will be dried under a stream of nitrogen and resuspended again in 50μL methanol/water (1:1) before injection into the LC-MS/MS system. The full method and acquisition LC-MS/MS parameters were previously published [30].

The remaining secondary variables were selected based on scientific literature [18,31–33]

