### Nutritional Intervention

Specialized Pro Resolving Mediators (SPMs) (17-HAD, 14-HAD and 18-HEPE) are a natural and standardized nutritional supplement selected to evaluate its efficacy in improving quality of life and other variables in patients with PCC after exposure after 12 weeks. The NG will receive the Nutritional supplement (500mg) enriched in SPMs, administered as 2 capsules after breakfast and 2 capsules after dinner. The Nutritional supplement with SPMs is a commercially available product. It contains an active fraction from fish oil, with standardized amounts of SPMs.

The PG will receive a placebo supplement composed of refined olive oil, gelatin and water which looks exactly like NG. The posology will be equal to the NG.

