#### Sample size calculation.

To estimate the sample size, a hypothesis test comparing the proportions of independent groups (PG vs. NG) assuming an alpha risk of 0.05 and a beta risk of 0.2 in a bilateral contrast requires 110 subjects in the placebo group and 110 subjects in the Nutritional supplement group to detect the difference in percentage of patients that will improve their EQ-5D-5L after intervention between the two groups, expected to be 30% and 50%, respectively, as statistically significant, and including a 15% loss estimated. Likewise, to assess the improvement in the pro inflammatory balance considering in this case the proportion of patients with change between pre-post intervention balances in each of the groups the estimated sample size will allow a difference of 20% or more between the two to be declared statistically significant, with a confidence level of 95% and a power of 80%. The estimation was carried out using the GRANMO sample size calculator, version 7.12 (Fig 3).

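### Compounds given as the supplement are listed among the inflammatory and pro-resolving outcomes without being set apart as exposure markers, and the balance is scored as a loosely worded proportion

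*Protocol article*

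**What the plan says.** The Nutritional Intervention section of the protocol article states: "Specialized Pro Resolving Mediators (SPMs) (17-HAD, 14-HAD and 18-HEPE) are a natural and standardized nutritional supplement". Of the commercial product it adds: "It contains an active fraction from fish oil, with standardized amounts of SPMs". The comparator is a "placebo supplement composed of refined olive oil, gelatin and water". The Abstract describes the daily intake as omega-3 or placebo.

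The Secondary outcomes section lists the analytes of the inflammatory and pro-resolving profile. They include "monohydroxylated lipid mediators (LMs): 17-HDHA, 18-HEPE, 14-HDHA" and the free fatty acids EPA and DHA. The same list holds nine cytokines, three prostaglandins, TXB2, LTB4 and the resolvins, maresins, protectins and lipoxins. Nothing marks any analyte as a measure of intake.

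The Sample size calculation section makes a second power statement, "to assess the improvement in the pro inflammatory balance considering in this case the proportion of patients with change between pre-post intervention balances". It claims 80% power for a difference of 20 percentage points or more. The Discussion expects quality-of-life gains in the supplement arm to be tied to a better inflammatory profile.

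**The concern.** One arm swallows these compounds every day for 12 weeks and the other takes olive oil. A between-arm difference in their blood levels is then the expected result of adherence. It would appear whether or not inflammation moved. The outcome list puts that difference next to IL-6, TNF-α, PGE2 and LTB4 as though all were evidence of the same kind.

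Two things follow. First, a significant rise in 17-HDHA, 14-HDHA, 18-HEPE, EPA or DHA could be reported as an improved profile and then used to explain a gain in quality of life. Second, if the balance includes these compounds, part of its improvement would be uptake. The responder wording adds to this: change is less specific than improvement, and turning a continuous laboratory quantity into a yes/no result discards information.

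**Working it through.** **1. Overlap of product and outcome.**

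| Named as the product (Nutritional Intervention) | Listed as outcome (Secondary outcomes) | Match |
|---|---|---|
| 18-HEPE | 18-HEPE | exact |
| 17-HAD | 17-HDHA | differs in abbreviation only; identity inferred |
| 14-HAD | 14-HDHA | differs in abbreviation only; identity inferred |
| fish-oil fraction; omega-3 in the Abstract | EPA, DHA | plausible; amounts not given |

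The profile has 9 + 4 + 3 + 2 + 5 + 2 + 2 + 2 + 3 + 1 + 1 = 34 analytes (cytokines, fatty acids, monohydroxylated mediators, E-resolvins, D-resolvins, maresins, protectins, lipoxins, prostaglandins, thromboxane, leukotriene). Three are the named product. Five are if EPA and DHA are added.

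**2. The plan's own figure.** For 30% against 50%, two-sided alpha 0.05 and power 0.80, the pooled formula gives

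n = [1.960·√(2·0.4·0.6) + 0.842·√(0.3·0.7 + 0.5·0.5)]² / 0.20² = 93 per arm,

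and 93/0.85 = 109.4, so 110 per arm. This reproduces. With 93 evaluable per arm, power for a 20-point difference is 78% to 97% for placebo rates from 5% to 70%. The 80% statement for the balance is therefore about right, and no number in that section is wrong.

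**3. What intake alone could do, if the compounds are in the balance.** The documents give no formula, so everything here is assumed:
- an equal-weight balance of k independent standardised changes;
- 30% responders on placebo;
- no effect on any other analyte;
- only the three named compounds shifted, each by s SD.

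The balance then shifts by 3s/√k SD, and the responder rate in the supplement arm is Φ(Φ⁻¹(0.30) + 3s/√k), with Φ⁻¹(0.30) = −0.524. For k = 34 and s = 1 the shift is 3/5.83 = 0.514, giving Φ(−0.010) = 50%.

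| Balance | s | Responders, supplement arm | Chance of p<0.05, 93 per arm |
|---|---|---|---|
| all 34 analytes | 0.5 | 40% | 27% |
| | 1 | 50% | 78% |
| | 2 | 69% | >99% |
| 9 cytokines + 3 compounds (12) | 0.5 | 46% | 63% |
| | 1 | 63% | >99% |
| | 2 | 89% | >99% |
| cytokines only | any | 30% | 5% |

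A false 20-point difference needs a shift of 0.524·√k/3 per compound: 1.02 SD for k = 34 and 0.61 SD for k = 12.

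**4. Cost of dichotomising.** The article gives no base rate for the balance, so the primary outcome's 30% and 50% are borrowed. On a normal scale with equal spread these rates are 0.524 SD apart. The continuous comparison at 93 per arm has power Φ(0.524·√(93/2) − 1.96) = Φ(3.58 − 1.96) = Φ(1.62), about 95%, against 80% for the proportions. This is before any gain from baseline adjustment.

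**The case against.** The heading of the outcome names pro-resolving as well as inflammatory analytes, so measuring these lipids is legitimate. Nine cytokines and several eicosanoids are listed too, and the planned between-group tests can be applied to each, so an absent anti-inflammatory effect could still be seen. The Discussion explains the expected mechanism largely through reduced cytokine production. The exact formula of a secondary balance is detail that an article may leave to the full protocol. All of this stands, and it keeps the point modest.

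A reader might infer more than the article supports:

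- **That the supplement arm will improve by construction.** No section places the administered compounds in the balance, and none calls it a ratio. With cytokines alone the error rate is nominal.
- **That everyone counts as changed, so the arms cannot be separated.** The same sentence speaks of improvement, which gives a direction. The wording is loose; it is not a rule that change in either direction counts.
- **That six analytes are supplied.** DPA is not named as a product component.
- **That 69% to 84% of the supplement arm would improve through intake.** Those rates are Φ(0.5) and Φ(1) against 50% on placebo. They need an assumed shift of the whole balance by 0.5 to 1 SD, for which the documents give no source.

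What the objection does not remove is the listing itself: product and outcome overlap, and nothing in the text separates uptake from effect.

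**Conclusion.** The point holds in a limited form. The article lists the compounds named as the supplement, with EPA and DHA, among the inflammatory and pro-resolving outcomes and does not separate them from inflammation read-outs. A between-arm difference in them may show only intake. It should not be read as improved inflammation or used to support the expected link with quality of life.

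For the balance, false improvement is a possibility that depends on an unstated formula. Under the assumptions above, the chance of a significant result without any effect on the other analytes runs from 27% to over 99% if the three compounds are included, and is 5% for a cytokine-only balance. The identity of 17-HAD and 14-HAD with 17-HDHA and 14-HDHA is inferred from near-identical names. Scoring the balance as a proportion costs power (about 95% down to 80% in the example). The stated sample size is correct, and the outcome is secondary.

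**What to change.** 1. Use one set of names for the compounds in the intervention and outcome sections.
2. Report 17-HDHA, 14-HDHA and 18-HEPE, with EPA and DHA, as exposure or adherence markers. They would complement the count of returned product. State that they are excluded from the efficacy balance.
3. Build the balance from listed analytes that are not administered, for example cytokines with PGE2, TXB2 and LTB4, and fix its formula and direction before unblinding.
4. Compare arms on the log of the balance at day 84 adjusted for its baseline value, in place of the proportion with change.

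Cost: wording only, if done before unblinding. The assays, visits and sample size stay the same. The price for the sponsor is that a likely significant difference in the administered compounds would be reported as uptake, not as efficacy.

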#### Fatigue.

Fatigue will be measured with the FSS [34], a self-reported scale that allows assessing the severity of fatigue as a sense of physical tiredness, muscle weakness and lack of energy. It has been validated in post-COVID patients [35]. It is composed of 9 items with scores ranging from 1= strongly disagree to 7= strongly agree. The higher the number, the greater the severity of fatigue. The most common cut-off point is a mean score of 4 points, considering equal or more than 4 as severe fatigue [36].

#### Dyspnea.

The dyspnea will be measured with the modified Medical Research Council (mMRC) [37]. This scale has already been used in other studies to assess the degree of dyspnea in post-COVID-19 patients [38]. This scale allows determining the magnitude of the dyspnea that the patient presents by scoring from 0 = absence of dyspnea to 4 = does not leave the house due to dyspnea.

#### Respiratory strength.

Measurements of maximum inspiratory pressure (MIP) and maximum expiratory pressure (MEP) can help evaluate respiratory muscle weakness in PCC patients [39]. This test is widely used to non-invasively evaluate respiratory muscle strength in clinical practice [40] and presents the cut-off point to detect muscle weakness for the Spanish population [41]. MIP/MEP will be measured based on the ATS/ERS 2002 guidance using the MicroRPM CareFusion pressure meter with individual antibacterial filters.

#### Functional status.

- 6MWT is a sub-maximal exercise test used and recommended to assess the maximum distance possible for six minutes, in a 30-meter corridor, allowing the patient to rest as needed. It has been shown to be reliable [42–44]. The distance covered by each participant will be compared with the estimated distance for their gender, weight, and age according to the Troosters equation [45].

- 30“STST is part of the Senior Fitness Test (SFT) designed by Rikli and Jones [46–48] and it will be used as a stand-alone test, especially to assess weakness in respiratory patients who have passed COVID-19 [49] and it has been shown to be reliable in adults with respiratory pathologies [50–53]. For the 30”STST, participants will sit in a chair with their feet flat on the floor and arms crossed over their shoulders, performing as many squats as possible within 30 seconds [47].

- 30“ACT is part of the SFT and is also used as a stand-alone test to assess strength. It has been shown to be reliable [51,52] in deconditioned patients and in the elderly population and used in Long COVID patients [31]. The higher number of repetitions the better strength [47,54]. During the 30”ACT, picipants will sit in a chair and perform as many elbow flexions as possible within 30 seconds using their dominant arm, with women lifting a 2 kg weight and men a 4 kg weight.

#### Psychosocial factors.

Psychosocial factors will be assessed by using Overall Anxiety and Depression Severity and Impairment Scales, OASIS and ODSIS, respectively. These scales have been used in studies with COVID-19 patients and have been validated in Spanish [55,56]. Both are two self-report questionnaires consisting of 5 and 9 items graduated in a Likert scale from 0= never to 4= all time, that assess the frequency, intensity, interference and severity of anxiety and depression on the activities of daily life. The total score range goes from 0 to 20, the highest score the highest involvement of anxiety or depression in patients. The cutoff scores will be the following: 15 points for OASIS and 12 for ODSIS.

#### Other outcomes.

**Clinics:** Comorbidities, COVID-19 diagnosis, initial symptoms, severity of infection, diagnosis, current treatment, vaccination, and blood data (hematology, coagulation, biochemistry) have already been registered in the ARACOV study (which was mentioned above).

#### Adherence.

Adherence to the telerehabilitation program will be recorded through the mobile application by pressing the “done” button for each exercise in the application itself. It will be coded as follows: 0= if the activity was not done, 1= if they have done some exercises that day, 2 = if they have all exercises that day. Those who complete more than 80% of the sessions (code 1 or 2) will be considered very adherent. “Non-adherent” will be understood as those who completed less than 20% of the sessions [57]. The rest will be considered “partially adherent.”

To evaluate adherence to the supplement, the patient will return the leftover product at last visit and the % adherence will be calculated according to the following formula: % Adherence = (Units taken/ Theoretical units to be taken in x days)*100. Patients will be considered adherent when the percentage adhesion is between 90–100%.

#### Sample size calculation.

To estimate the sample size, a hypothesis test comparing the proportions of independent groups (PG vs. NG) assuming an alpha risk of 0.05 and a beta risk of 0.2 in a bilateral contrast requires 110 subjects in the placebo group and 110 subjects in the Nutritional supplement group to detect the difference in percentage of patients that will improve their EQ-5D-5L after intervention between the two groups, expected to be 30% and 50%, respectively, as statistically significant, and including a 15% loss estimated. Likewise, to assess the improvement in the pro inflammatory balance considering in this case the proportion of patients with change between pre-post intervention balances in each of the groups the estimated sample size will allow a difference of 20% or more between the two to be declared statistically significant, with a confidence level of 95% and a power of 80%. The estimation was carried out using the GRANMO sample size calculator, version 7.12 (Fig 3).

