### Outcome measures

#### Primary outcome: Quality of life: EQ-5D-5L.

The EQ-5D-5L is a generic instrument for measuring health-related quality of life that has been validated [23] in Spanish and in PCC patients. It consists of two components: the levels of severity by dimensions and a visual analogue scale (VAS) on general health. The descriptive system contains five dimensions of health (mobility, self-care, activities of daily living, pain/discomfort, and anxiety/depression) and each of them has five levels of severity (From 1=No problem to 5=unable to perform). Participants indicate their perceived overall health on a VAS from 0 (“worst health I can imagine”) to 100 (“best health I can imagine”). The values obtained will be compared with the reference values [24]. Quality of life will be analyzed as a continuous variable by comparing the relevant statistics according to their distribution at the two points in time and as a qualitative variable by comparing the percentage of patients who improve their scores.

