#### Statistical analysis.

Statistical analysis will be performed with IBM-SPSS Statistics software version 25 or later. Quantitative variables will be described as mean and standard deviation (SD) if the variable follows a normal distribution or as median and interquartile range for non-normal data. For categorical data absolute and relative frequencies will be computed. The Kolmogorov-Smirnov test will be used to determine the normality of the data. Intra-group variables will be measured with the T-Student test for related samples or the paired samples Wilcoxon test for non-parametric alternative. For inter-group comparations non-parametric analysis will be performed when a non-normal distribution is assumed, using the U Mann Whiney test for comparisons between groups and T-Student test for normal data. Dichotomous variables will be analyzed using the chi-square test. A significant level of 95% will be assumed (p <0.05). If there are more than 15% dropouts, an intention-to treat (ITT) analysis will be performed. Effect size will be calculated using Cohen’s d to determine clinical significance: negligible, small, medium and large differences will be reflected in effect sizes of < 0.2, 0.2–0.5, 0.6–0.8 and > 0.8, respectively.

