## Discussion

Based on our literature review, this is the first study that will combine a dietary supplement based on SPMs with telerehabilitation to reduce the symptoms of patients with PCC. The effectiveness of a nutritional over only a physiotherapeutic intervention would open a field of intervention for these patients who still do not have an effective treatment.

Statistical improvements in quality of life are expected in the Nutritional supplement group to be linked to the improvement of the inflammatory profile although changes are expected in both groups. Specialized nutrition with SPMs might have favorable effects on PCC symptoms due to the potential mechanisms of action for omega-3 acids and their metabolites [25,58]. These actions will result in clinical improvement and therefore in the quality of life perceived by patients. In this regard, Pavlidou’s review confirms that this type of supplementation is beneficial before and during COVID-19 disease and encourages studies like this one to show its effect in patients with PCC [59]. In addition to the nutritional supplement, pulmonary rehabilitation and controlled aerobic and strength training seem to be the most effective interventions used to improve the symptoms of PCC [60]. Furthermore, telerehabilitation has already been shown to be effective in improving quality of life in a similar way to face-to-face treatments, as reported by Dias et al. 2021 in a systematic review [61].

It is expected to have a reduction of long-lasting inflammation in NG for the anti-inflammatory effect of omega-3 [62] by blocking the inflammasome activation and pro-inflammatory cytokine production, thereby restoring tissue homeostasis; improving innate immunity; and reducing oxidative stress by controlling the activity of related enzymes and the generation of free radicals (ROS) [63]. Although the effectiveness of SPMs in reducing inflammation in these patients is not yet proven, in vitro studies show that both Resolvin D1 and Resolvin D2 are potent in reducing the production of pro-inflammatory cytokines, showing the potential role of lipid mediators in the treatment of PCC [64]. The favorable effects of physical exercise on the reduction of inflammation, as well as the modulation of cytokines, have been widely reported in different fields [65,66]. Therefore, improvements can be expected in both groups, although NG will show greater changes, due to the sum of two interventions with anti-inflammatory potential.

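### The trial is sized on an undefined EQ-5D-5L responder, and the only form of the primary outcome given a power claim is weaker than the continuous comparison also planned

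*Protocol article*

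**What the plan says.** The sample size section tests two independent proportions, "assuming an alpha risk of 0.05 and a beta risk of 0.2 in a bilateral contrast". The trial is sized "to detect the difference in percentage of patients that will improve their EQ-5D-5L after intervention between the two groups", with group rates "expected to be 30% and 50%, respectively" for placebo and supplement. It "requires 110 subjects in the placebo group and 110 subjects in the Nutritional supplement group", "including a 15% loss estimated". No source is given for the two rates.

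The primary outcome section describes two parts of the instrument: five dimensions with five levels each, and a 0 to 100 visual analogue scale (VAS). Quality of life is then to be analysed in two ways: as a continuous variable, and as a qualitative one by "comparing the percentage of patients who improve their scores". Nothing there says which part must improve, by how much, or which of the two analyses is primary.

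The Discussion predicts better quality of life in the supplement group, "although changes are expected in both groups". The statistical analysis section offers unadjusted between-group tests (t-test or Mann-Whitney, chi-square for dichotomous variables) and judges clinical significance by Cohen's d.

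**The concern.** The event behind the only power statement for the primary outcome is not defined. Read literally, any upward move on any EQ-5D-5L score is a response, so small random fluctuations count as much as real gains. The reader cannot tell which quantity the 30% and 50% describe, and so cannot judge whether they are realistic.

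There is also a question of efficiency. The same patients supply a continuous score, which carries more information than a yes/no split. If the responder comparison is the primary test, the trial gives up power that it could have at no extra cost. Because both analyses are listed without a choice between them, the result reported as primary could also be chosen after the data are seen.

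**Working it through.** **Inputs from the protocol article.** Two-sided alpha 0.05, power 0.80, p1 = 0.30, p2 = 0.50 and loss 15% (sample size section); 1:1 allocation (allocation section). The article gives no SD, share of unchanged patients or distribution of change, so steps 2 to 4 rest on stated assumptions.

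**1. The plan's own figure.** Pooled-variance formula without continuity correction, with mean rate p = 0.40:

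n = [1.960·√(2·0.40·0.60) + 0.842·√(0.30·0.70 + 0.50·0.50)]² / 0.20²
= (1.358 + 0.571)² / 0.04 = 93 per arm.

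93/0.85 = 109.4, so 110 per arm. The stated figure reproduces.

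**2. What a 30% placebo rate implies if any gain counts.**

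- With no net change and a share k of patients unchanged, the improved share is (1 − k)/2. This gives 50% at k = 0, 45% at 10%, 40% at 20%, 35% at 30% and 30% at 40%.
- With few ties and a normal change, a 30% improved share means a placebo mean change of z(0.30) = −0.52 SD, which is a worsening.
- If placebo patients improve on average, the unchanged share has to be larger. With a normal change and a symmetric no-change band, it is about 52% for a mean gain of 0.2 SD and about 64% for 0.5 SD.

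**3. Responder test against continuous score at the planned effect.** Assume equal spread in both arms and one common cut-off producing 30% and 50%.

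- Normal scale: d = z(0.50) − z(0.30) = 0 + 0.524 = 0.524.
- Logistic scale: ln(OR) = ln[(0.5/0.5)/(0.3/0.7)] = 0.847; d = 0.847·√3/π = 0.467.

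With 93 evaluable per arm:

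| Analysis | Power |
|---|---|
| Responder, 30% v 50% | 80.0% |
| t-test, d = 0.524 | 94.5% |
| t-test, d = 0.467 | 88.6% |

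On the normal scale, the continuous score needs 2·[(1.960 + 0.842)/0.524]² = 57.1, so 58 evaluable per arm (69 with 15% loss), against 93 (110) for the responder.

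**4. Does a minimum gain restore the power?** Normal change, d = 0.524, placebo mean change 0, 93 per arm:

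| Cut-off | Placebo / supplement | Power |
|---|---|---|
| 0 (any gain) | 50% / 70% | 80.0% |
| 0.5 SD | 31% / 51% | 80.2% |
| 1.0 SD | 16% / 32% | 72.2% |

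It does not. The loss comes from splitting the score, not from where it is split.

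**5. How much does a wrong placebo rate cost?** At the same d, with any gain counting:

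| Placebo mean gain | Placebo / supplement | Power |
|---|---|---|
| 0.2 SD | 58% / 77% | 77.7% |
| 0.3 SD | 62% / 79.5% | 76.0% |
| 0.5 SD | 69% / 85% | 71.6% |

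If the 20-point difference itself holds, power stays between 78% and 85% for placebo rates from 20% to 60%.

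**The case against.** **The rates may be right.** A reader might infer that 30% and 50% are incompatible with an any-gain definition. The document does not show that. The VAS is not named as the responder score, and on coarse five-level dimensions many patients may be unchanged; about 40% unchanged gives a 30% placebo rate with no net change. What stands is weaker: the rates are unsourced, and they sit uneasily with the change expected in both groups unless the unchanged share is large.

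**The missing threshold does not cause the power loss.** This is correct, as step 4 shows.

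**Power is not shown to collapse.** A reader could obtain responder power of 50% to 57% by assuming a true shift of 0.4 SD. That shift is not in the document, and it causes most of the drop: with the placebo rate held at the planned 30%, power at 0.4 SD is already 56%, and the continuous test also falls, to 77%. No such figure should be attached to this plan.

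**The continuous analysis is already planned.** True, and it means the power is lost only if the responder comparison is the primary test. But the article does not choose, and its power claim covers only the responder form.

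**Noise is not bias.** In a randomised double-blind comparison, random upward moves occur in both arms alike. They dilute a difference and do not create one.

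**A cut-off may be left to the full protocol or analysis plan.** That is fair for the cut-off taken alone. Here, though, the article fixes the rates, error levels, loss and sample size for an event it does not identify.

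**Cohen's d.** The bands ("reflected in effect sizes of < 0.2, 0.2–0.5, 0.6–0.8 and > 0.8") leave 0.5 to 0.6 unclassified. This is a small drafting gap with no effect on the sample size or the primary test.

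**Conclusion.** The point holds in a limited form. The event that sizes the trial has no minimum gain, no named score and no stated rank against the continuous analysis. The 110 per arm is arithmetically correct for 30% versus 50%, but those rates are unsupported.

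At the planned effect, the responder test has 80% power where a continuous comparison in the same 93 evaluable patients per arm would have about 89% to 94%. That range rests on a logistic or normal change with equal spread and a common cut-off. The protocol itself allows for non-normal data, so the gain is indicative.

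The document does not support the stronger readings: that the rates are shown to be wrong, that the absent threshold is what costs power, or that true power is near 50%. This is a change that should be made; it does not invalidate the design.

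**What to change.** Before unblinding:

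1. Name one EQ-5D-5L score as the primary variable (for example a derived index or the VAS).
2. Make the between-arm comparison of that score at the final visit, adjusted for baseline, the single primary analysis. Keep 220 patients.
3. Restate the power sentence for that analysis, giving the assumed shift, SD and distribution, and the source of each.
4. Keep the responder analysis as secondary. Define response as a gain of at least a pre-specified minimal important difference for the named score, and report a risk difference with 95% CI.
5. Judge clinical relevance against that difference. If Cohen's d stays, close the gap between 0.5 and 0.6.

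**Cost.** No extra patients or data. The protocol, analysis plan and registry entry must change at a late stage: the article expects enrolment to finish by the end of 2024 and data collection by April 2025. This alters the status of the primary analysis as well as its wording, so it should be dated and shown to precede unblinding. The responder rate will be lower than under an any-gain reading.
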